## **Control group**

Patients in the conventional treatment group were required to complete the SAS,SDS,AFQ-18 and MARS5 scales during hospitalization and 3 months after

discharge, and received normal doctor-nurse communication and standardized treatment during hospitalization. Standardized treatment was carried out in strict accordance with the Chinese guidelines for the management of AF. In addition, all AF patients were provided with lifestyle advice to reduce the risk factors of AF through oral education by physicians.

## **Randomization**

The study employed an online randomization tool to allocate 208 patients undergoing radio-frequency ablation into either the digital animation intervention group or the usual care group with equal probability. Stratification based on gender and age ( $>60$  or  $\leq 60$  years) was conducted to ensure balance in baseline characteristics between the two groups.

## **Blinding**

Neither the participants, treating clinicians, nor the researchers were blinded.

## **Study Outcome**

Two groups at baseline and 3 months after discharge to check twice. Evaluation index including 3 months after the quality of life score (self-rating anxiety scale [SAS], self-rating depression scale [SDS], the quality of life in patients with AF [AFQ-18] and medication Adherence Report Scale [MARS5]).

All patients with AF included in the study, regardless of whether they were assigned to the intervention group or the control group, the above experimental results were only collected at admission and the 3-month follow-up after discharge. There was no follow-up and no telephone intervention during the 3-month period after discharge.

## **Statistical Method:**

Statistical analyses were conducted using SPSS 23.0 and R software version 4.2.2. For data that followed a normal distribution, means  $\pm$  standard deviations ( $\pm$ SD) were used for representation, and comparisons between the two groups were made using the independent samples t-test. For data that did not follow a normal distribution,

medians and interquartile ranges (IQR) were used, with the Mann-Whitney U test applied to analyze differences between groups. Categorical data were expressed in numbers and percentages, and compared using the chi-square test or Fisher's exact test as appropriate. To assess the effectiveness of the intervention, differences between the two groups were calculated by subtracting the change from baseline to 3 months in the control group from that in the intervention group. An independent t-test was then conducted to determine differences between groups before and after the intervention. A p-value of less than 0.05 was considered statistically significant.

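### The effect is tested by an unadjusted t-test on change scores: valid under randomisation, but generally less precise than a model with the baseline score and the stratification factors as covariates

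*Combined protocol and SAP*

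**What the plan says.** The Statistical Method section gives general rules for describing and comparing data: a t-test for normal data, medians and IQRs "with the Mann-Whitney U test applied to analyze differences between groups" for non-normal data, and chi-square or Fisher tests for categorical data. It then turns to effectiveness, which is measured by "subtracting the change from baseline to 3 months in the control group from that in the intervention group". The test follows directly: "An independent t-test was then conducted to determine differences between groups before and after the intervention". No regression, ANCOVA, mixed model or stratified test appears anywhere in the document.

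Two other sections matter here.

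- **Randomization:** allocation was 1:1 for 208 patients, with "Stratification based on gender and age" (cut at 60 years).
- **Study Outcome:** all four scales (AF-QoL-18, also written AFQ-18, plus SAS, SDS and MARS5) have exactly two measurements, since "the above experimental results were only collected at admission and the 3-month follow-up after discharge".

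Every covariate for an adjusted analysis is therefore already collected.

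**The concern.** A change score uses the baseline with a coefficient fixed at 1. When the correlation between visits is moderate and the SDs are similar, the best coefficient is below 1, so subtraction corrects too much. This has two consequences.

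- The standard error is larger than it need be.
- A patient group that happens to start lower tends to show more improvement through regression to the mean, and the change-score contrast carries that into the estimated effect. Randomisation is stratified on gender and age but not on the baseline scores, so the design does not control such an imbalance.

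Leaving the stratification factors out has a separate effect. Stratified allocation removes between-stratum variation from the treatment contrast, but an unadjusted t-test still counts it in the standard error. If gender or age predicts change, the test is then conservative.

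At stake is the chance of detecting a real effect on quality of life, the primary objective, with the patients already enrolled.

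**Working it through.** **1. The plan's own figure.** Sample Size Consideration states 80 assessable patients per group, from a comparison of two proportions 20 points apart with 90% power and α = 2.5%. This cannot be confirmed, because no control proportion is given and the ICC has no cluster size. At one-sided 0.025 (equivalent to two-sided 0.05), the two-proportion formula gives 65, 82, 109 and 130 per arm at control proportions of 5%, 10%, 20% and 40%. With 80% retention, 80/0.8 = 100 per arm, or 200 in total, which the 208 randomised cover. I use 80 per arm below only as the planned number of evaluable patients. It says nothing about the precision of a continuous score.

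**2. Inputs.**
- From the documents: 1:1 allocation, 80 evaluable per arm, a 0.05 threshold (taken as two-sided; the plan does not say).
- Assumed: the within-arm correlation r between baseline and 3 months (range 0.3 to 0.9), equal SDs at the two visits, and a true difference of 0.4 SD of the raw score.

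**3. Variance.** With raw SD = 1, the per-patient variance is 2(1−r) for the change score and 1−r² for ANCOVA. The ratio is (1−r²)/[2(1−r)] = (1+r)/2. Power is by the non-central t distribution at 80 per arm.

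| r | Change 2(1−r) | ANCOVA 1−r² | Ratio | Power, change | Power, ANCOVA |
|---|---|---|---|---|---|
| 0.3 | 1.40 | 0.91 | 0.65 | 57% | 75% |
| 0.5 | 1.00 | 0.75 | 0.75 | 71% | 83% |
| 0.7 | 0.60 | 0.51 | 0.85 | 90% | 94% |
| 0.9 | 0.20 | 0.19 | 0.95 | above 99% | above 99% |

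Inverting the ratio, the change score carries 54%, 33%, 18% and 5% more variance. At r = 0.5 the difference detectable with 90% power is 0.516 SD for the change score and 0.447 SD for ANCOVA.

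**4. The same gain without assuming an effect size.** Take 104 × 0.8 ≈ 83 evaluable per arm, and whatever effect gives the change-score test 80% power. ANCOVA then has 93.5%, 89.9%, 86.0% and 82.0% power at r = 0.3, 0.5, 0.7 and 0.9. It matches the precision of 166 patients on change scores with about 108, 125, 142 and 158.

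**5. Unequal SDs.** Let s0 and s1 be the SDs at baseline and 3 months. Then

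Var(change) − Var(ANCOVA) = (s0² + s1² − 2r·s0·s1) − s1²(1−r²) = (s0 − r·s1)².

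In large samples this is never negative, but it is zero when r·s1 = s0. Example: s0 = 1, s1 = 1.25 and r = 0.8 give 1 + 1.5625 − 2 = 0.5625 for the change score and 1.5625 × 0.36 = 0.5625 for ANCOVA.

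**6. Chance imbalance.** With equal SDs, a baseline difference d between arms shifts the change-score contrast by (r−1)d. For d = 0.2 SD and r = 0.5 the shift is 0.10 SD in size. The standard error is √(1.00 × 2/80) = 0.158 SD. ANCOVA removes this shift.

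**7. Strata.** Simulation with 160 patients, four equal strata balanced within stratum, and r = 0.5:

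| Share of change-score variance explained by strata | Type I error, t-test | Type I error, adjusted | Power, t-test | Power, adjusted |
|---|---|---|---|---|
| 0% | 5.3% | 5.1% | 79% | 90% |
| 5% | 4.5% | 5.1% | 81% | 91% |
| 10% | 4.2% | 5.3% | 80% | 92% |
| 20% | 2.8% | 4.8% | not run | not run |

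The unadjusted test becomes conservative as the strata become predictive. The power gap is already present when the strata explain nothing, so nearly all of it comes from the baseline term.

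**The case against.** The strongest reply is that nothing here is invalid. The change-score contrast is unbiased under randomisation, its type I error is not inflated, and it is easy to explain. The gain cannot be read from the trial, because r, the SDs and the effect are all assumed. At r = 0.9 it is 5% of variance, and with certain unequal SDs it is nil. A gender or age effect that is the same at both visits cancels in a change score, so the strata matter only if they predict change. Finally, the text is in the past tense and the trial is unblinded. If the data have been seen, replacing the stated test would be a post hoc change of primary analysis.

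All of that stands. It limits the point to efficiency and to accuracy given the baseline actually observed, and it shapes the fix. It does not remove the point: in large samples adjustment is never less precise, at the price of a few degrees of freedom, and the data are in hand.

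A reader might infer three stronger things that the documents do not support.

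- **That the baseline score is ignored.** It is subtracted from every outcome; only its coefficient is fixed.
- **That ANCOVA gains at every correlation below 1.** That needs equal SDs (step 5).
- **That the primary p-value is left open between the t-test and Mann-Whitney.** The effectiveness sentence names the t-test with no normality condition, and it can naturally be read as fixing that test. At most, a sentence is needed to say that the general rule for non-normal data does not reach it.

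**Conclusion.** The point holds as a matter of precision. The planned analysis uses an unadjusted t-test on change scores, with the baseline coefficient fixed at 1 and the stratification factors left out. With equal SDs, the change score has 5% to 54% more variance than ANCOVA for r from 0.9 to 0.3. At 80 per arm and an assumed 0.4 SD difference, this costs 18, 12 and 4 percentage points of power at r = 0.3, 0.5 and 0.7. These sizes rest on assumptions that the documents neither give nor contradict. The gain could be smaller, or zero, if the SD rises between visits while r is high.

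This is not a finding of bias or of excess false positives. Sensitivity to baseline imbalance means that a particular estimate can be pulled by chance, not that the method is wrong on average. The contribution of the strata is secondary and can only make the planned test conservative. The change is worth making because it is nearly free.

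**What to change.** Analyse 3-month AF-QoL-18 with a linear model on arm, baseline AF-QoL-18, gender and age group (>60 or ≤60). Report the adjusted mean difference with its 95% CI. Use robust or bootstrap standard errors if the residuals are skewed, rather than switching tests. Use the same model for SAS, SDS and MARS5, each with its own baseline. Keep the change-score t-test as a sensitivity analysis.

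Before outcome data are seen, the cost is a paragraph in the plan and a few lines of code, with no new patients, visits or measurements. If outcome data have already been seen, keep the planned t-test in place, report the adjusted model beside it, and label the model as added later.

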### **Sample Size Consideration**

The sample size estimation was based on a comparison of two independent proportions, with a Type I error rate ( $\alpha$ ) set at 2.5%, an intra-cluster correlation coefficient (ICC) of 0.01, and an anticipated retention rate of 80%. Our objective is to detect a significant absolute difference of 20% in clinical outcome between the intervention and standard treatment groups with a statistical power of 90% at a follow-up period of 3 months. Based on our calculations, it is determined that a minimum sample size of 80 assessable patients per group is required to achieve this desired level of statistical power.

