## **Study Purpose**

**Primary Objective:** To assess the improvement in quality of life among patients with AFCA three months post-discharge.

**Secondary Objectives:** To evaluate the changes in anxiety, depression, and medication adherence among patients with AFCA three months after discharge.

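### The stated 90% power is for a difference between two proportions with a cluster correlation, not for the planned t-test on change in quality-of-life score, and the 80 per group cannot be reproduced.

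*Combined protocol and SAP*

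**What the plan says.** - **Sizing.** Sample Size Consideration: "The sample size estimation was based on a comparison of two independent proportions". The target is "a significant absolute difference of 20% in clinical outcome between the intervention and standard treatment groups", with 90% power at 3 months. The Type I error rate is "set at 2.5%, an intra-cluster correlation coefficient (ICC) of 0.01", and 80% retention is expected. The result is "a minimum sample size of 80 assessable patients per group is required to achieve this desired level of statistical power". The outcome is not named. No control rate, sidedness, cluster unit or cluster size is given.
- **Objective.** Study Purpose, primary objective: "To assess the improvement in quality of life among patients with AFCA three months post-discharge".
- **Outcome.** Study Outcome lists questionnaire scores (SAS, SDS, AFQ-18, MARS5) at baseline and 3 months. No cut-off turns any of them into a responder status.
- **Design.** Randomization allocates 208 individual patients with equal probability, stratified by gender and age. Study Design places the trial at one hospital.
- **Analysis.** Statistical Method takes the change from baseline in each arm and the difference between arms. "An independent t-test was then conducted to determine differences between groups before and after the intervention". The significance threshold is p < 0.05, and no clustering term appears.

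**The concern.** A power statement has meaning only for the endpoint type, design and test for which it was computed. Here all three differ from the primary analysis: a proportion against a score, a clustered design against individual randomisation, and a two-proportion comparison against a t-test on change.

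This section is the only place where the plan says what effect the trial was built to find. As it stands, a reader cannot tell what difference in quality-of-life score the trial could detect. A null result might then be read as evidence of no effect backed by 90% power, when that figure belongs to another comparison.

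**Working it through.** **1. Can the 80 be reproduced?**

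Inputs from Sample Size Consideration: difference 0.20, power 90% (z = 1.2816), alpha 2.5%. I read alpha as one-sided (z = 1.960), because that matches two-sided 5% in Statistical Method. The control rate p1 is not given, so I scan it as an assumption, with p2 = p1 + 0.20. The ICC is set aside at this step.

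Pooled formula, with p̄ the mean of p1 and p2:

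n per group = [1.960 × √(2p̄(1−p̄)) + 1.2816 × √(p1(1−p1) + p2(1−p2))]² / 0.20²

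Power at 80 = Φ{[0.20 × √80 − 1.960 × √(2p̄(1−p̄))] / √(p1(1−p1) + p2(1−p2))}

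Example, 10% v 30%: (1.960 × 0.5657 + 1.2816 × 0.5477)² / 0.04 = 1.8107² / 0.04 = 82.0.

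Example, power at 40% v 60%: (1.7889 − 1.960 × 0.7071) / 0.6928 = 0.58, and Φ(0.58) = 72%.

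| Assumed rates | n per group for 90% | Power at 80 per group |
|---|---|---|
| 5% v 25%, or 75% v 95% | 64.9 | 95% |
| 10% v 30%, or 70% v 90% | 82.0 | 89% |
| 20% v 40%, or 60% v 80% | 108.2 | 79% |
| 30% v 50%, or 50% v 70% | 124.0 | 74% |
| 40% v 60% | 129.3 | 72% |

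The exact boundary depends on the formula. The unpooled version gives 78.8 at 10% v 30%, so 80 suffices there; the pooled version just misses. Either way, 80 fits only at control rates of about 10% or lower, or about 70% or higher.

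**2. The ICC.** A design effect is 1 + (m − 1) × 0.01 for cluster size m. No m is given, so it cannot be computed. Any m above 1 would raise the numbers in the table. With individual randomisation and no cluster term in the analysis, the plan offers nothing to which it applies.

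**3. Retention.** 80 / 0.80 = 100 per arm. With 208 randomised, 104 per arm × 0.80 = 83.2 assessable. This part is consistent.

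**4. What the planned test can detect.** No SD or target mean difference is given, so the result is in SD units of the change score.

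Normal approximation, two-sided 5%, 90% power, 80 per arm: d = (1.960 + 1.2816) × √(2/80) = 0.513. The exact (non-central t) value is 0.516. At 83 per arm it is 0.506.

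Exact power at 80 per arm, for assumed true differences:

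| Difference (SD of change) | Power |
|---|---|
| 0.3 | 47% |
| 0.4 | 71% |
| 0.5 | 88% |
| 0.516 | 90% |
| 0.6 | 97% |

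**The case against.** The other side has several fair points.

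- **No arithmetic slip is shown.** Some control rates do lead to 80, and the retention allowance fits 208. This stands. The defect is a mismatch between sizing and analysis, with inputs missing.
- **Proportions are not absent from the plan.** Statistical Method provides chi-square or Fisher tests for categorical data, and Study Design follows smoking, drinking and similar habits to 3 months. This stands, so one cannot say that the trial analyses no proportion. But none is named in the primary or secondary objectives, and no score has a responder definition.
- **The primary variable is itself loosely defined.** Study Purpose says only quality of life, and Study Outcome groups four scales under a quality-of-life score. AF-QoL-18 (AFQ-18) is the natural reading, but it is an inference. The mismatch does not depend on it, because all four are scores.
- **Alpha may not conflict.** One-sided 2.5% equals two-sided 5%. A reader might infer a contradiction with p < 0.05, but the documents show only that sidedness is unstated. I therefore draw no shortfall from a two-sided 2.5% reading.
- **Nothing in conduct or analysis changes.** No patient or estimate is affected, and a reported confidence interval would limit over-reading of a null result. This reduces the harm, but leaves the power statement wrong as written.

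**Conclusion.** The point holds. The 90% power belongs to a comparison that the plan does not make for its primary objective, and the figure of 80 cannot be reproduced from the stated inputs. Even for two proportions, 80 per group delivers about 72% to 74% power at assumed control rates of 30% to 40%, with 2.5% taken as one-sided and no design effect.

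A reader might go further and infer that the trial is underpowered. The documents do not support that. They give neither an SD nor a target difference. At 80 evaluable per arm, the planned test has about 90% power if the true difference is about 0.52 SD of the change score, and less if it is smaller. Which case applies cannot be determined from the plan.

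**What to change.** Amend Sample Size Consideration as follows.

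1. Confirm the change in AF-QoL-18 (AFQ-18) score as the primary variable, if that is what is meant.
2. State that the 90% power figure and the ICC of 0.01 do not apply to the primary t-test.
3. Add a statement along these lines: *Retrospective sensitivity statement: 80 evaluable patients per arm give 90% power, at two-sided alpha 0.05, for a between-arm difference of about 0.52 SD of the change score (about 0.51 SD at 83 per arm). Power is about 71% at 0.4 SD and 47% at 0.3 SD.*
4. Keep the two-proportion basis for 80 on record, marked as superseded. Study Design gives recruitment as running from January 2022 to August 2023, and the text is in the past tense. A difference solved backwards from 80 must not be presented as the planned target.
5. State the sidedness of alpha so that it matches p < 0.05 in Statistical Method.
6. If the detectable difference is converted to scale points, name the source of the SD.

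The cost is one paragraph and a less favourable stated sensitivity. The 208 patients and the analysis stay as they are.

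### The plan expects 20% loss, but its effectiveness test can use only patients with both scores, and it gives no analysis set or missing-data sensitivity analysis, so loss that differs by arm could bias the result

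*Combined protocol and SAP*

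**What the plan says.** Under Sample Size Consideration, the combined protocol and SAP assumes "an anticipated retention rate of 80" percent and asks for "a minimum sample size of 80 assessable patients per group". Randomization gives 208 patients allocated with equal probability.

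Statistical Method defines the effect as the between-arm difference in change from baseline to 3 months, and continues: "An independent t-test was then conducted to determine differences between groups before and after the intervention". Mann-Whitney, chi-square and Fisher tests are also named for group comparisons, but none of them deals with a missing score. The decision rule is "A p-value of less than 0.05 was considered statistically significant".

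Study Outcome limits the scales to admission and the 3-month contact: "There was no follow-up and no telephone intervention during the 3-month period after discharge". Study Design says that this contact is by telephone, and Blinding says that nobody was blinded.

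No section defines an analysis population, a method for missing scores, a missing-data sensitivity analysis, or reporting of loss and reasons by arm.

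**The concern.** A patient without a 3-month score has no change value and cannot enter the t-test. Followed as written, the plan therefore gives an unadjusted comparison of those who answered the 3-month call. The 80% retention figure is used only to secure numbers. It protects power and does nothing about who is missing.

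There are reasons to expect loss to differ by arm. Patients know their allocation. Only the intervention arm had repeated accompanied sessions in hospital. The outcomes are quality of life, anxiety, depression and adherence, which may influence whether someone takes part in a follow-up call. No intermediate score exists to show how lost patients were faring. If the arms lose different kinds of patients, or different numbers of patients who differ from those retained, the estimated effect mixes the intervention with selection.

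**Working it through.** **Inputs from the plan:** 208 randomised 1:1 (Randomization), 80% retention and 80 assessable per group (Sample Size Consideration), test on change at 0.05 (Statistical Method; taken as two-sided, which the plan does not state). **Not in the plan, so assumed:** loss by arm, SDs, the gap between lost and retained patients, and the correlation between baseline and 3 months.

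**Numbers.**
- 80 / 0.80 = 100 per arm, or 200 in total. The 208 randomised covers this.
- 208 × 0.20 = 41.6, about 42 patients without a change score.
- 104 × 0.80 = 83.2 per arm retained, above the required 80.

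The 80 itself cannot be re-derived, because the control proportion and cluster size are not given. That is a separate matter.

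**Bias formula.** In each arm, the mean over all patients = mean of those retained + L × G. L is the proportion lost and G is the mean change of lost minus retained patients. With T for intervention and C for control:

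true difference − completer difference = L_T × G_T − L_C × G_C.

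Take a scale on which higher is better, in SDs of change.

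- *Same rate, same gap* (20% in each arm, G = −0.5): 0.20 × (−0.5) − 0.20 × (−0.5) = 0. No bias.
- *Different rate, same gap* (25% against 15%): size = 0.10 × 0.5 = 0.05 SD, or 0.10 × 1.0 = 0.10 SD. It favours the intervention if that arm loses more patients and counts against it if the control arm does.
- *Same rate, gap in the intervention arm only* (20% each): 0.20 × 0.5 = 0.10 SD, or 0.20 × 1.0 = 0.20 SD, in favour of the intervention.

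**Type I error.** SE = √(2/n) = 0.158 SD at 80 per arm and 0.155 at 83. The two-sided error is 1 − Φ(1.96 − bias/SE) + Φ(−1.96 − bias/SE).

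| Bias (SD) | 80 per arm | 83 per arm |
|---|---|---|
| 0 | 5.0% | 5.0% |
| 0.05 | 6.2% | 6.2% |
| 0.10 | 9.7% | 9.9% |
| 0.20 | 24% | 25% |

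**Which analysis helps, and when.** Simulation with no true effect: 2,000 trials per row, 104 per arm, about 20% loss, correlation 0.5 between baseline and 3 months (assumed). The entries are type I error, with bias in SDs where it is not close to 0.

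| Loss mechanism | Change t-test | Baseline-adjusted model |
|---|---|---|
| At random | 5.7% | 4.9% |
| Related to baseline, same in both arms | 4.7% | 4.5% |
| Related to baseline, opposite by arm | 21% (0.18) | 5.6% (0.00) |
| Related to 3-month score, same in both arms | 4.5% | 5.1% |
| Related to 3-month score, intervention arm only | 8.9% (0.09) | 18.6% (0.14) |

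A separate simulation of the last row, adding multiple imputation by arm from the baseline score, gave 8.4% (bias 0.09) for the change t-test, 17.4% (0.14) for the adjusted model and 17.6% (0.14) for imputation followed by the adjusted model. Subtracting the full baseline score happens to cancel more of this selection than adjusting for it does. Baseline adjustment therefore cures loss explained by baseline, but not loss that depends on the unseen 3-month score.

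**The case against.** The strongest reply is that a randomised comparison tolerates a good deal of loss. A reader might infer that the result is valid only if loss is unrelated to outcome. Neither the plan nor the arithmetic supports that: when loss depends on outcome equally in both arms, the bias is nil and the error stays near 5%. This stands, and it confines the point to loss that differs by arm.

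It can also be said that the 80% is a planning allowance, that actual loss is not reported, and that the 25% against 15% split and the 0.5 to 1.0 SD gap are in no section. All of this is true. At the low end the error is 6.2% instead of 5%, which is minor.

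A reader might also infer that multiple imputation from baseline would settle the matter. It would not. With no intermediate scores, it leans on baseline alone, and where loss depends on the 3-month score in one arm it can do worse than the planned t-test.

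Finally, the plan never says in words that only completers are analysed. That follows from the form of the test and the absence of any other rule.

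What none of this removes is the gap itself: a fifth of patients expected to be lost, a test that cannot use them, and nothing to show whether the conclusion depends on them.

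**Conclusion.** The point holds as a gap in the analysis plan, not as proof of a biased result. About 42 of 208 patients are expected to be missing from the effectiveness test, and loss that differs by arm, in rate or in its relation to baseline or outcome, could bias it in either direction.

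The size cannot be fixed from the plan. The illustration of 0.05 to 0.10 SD, with type I error of 6% to 10%, rests on assumed loss of 25% against 15% and the same assumed 0.5 to 1.0 SD gap in both arms. Equal 20% loss with that gap in the intervention arm only would give 0.10 to 0.20 SD and about 10% to 25%. If actual loss was small, or alike in both arms, the harm is small or absent. The change is worth making because it is cheap and uses data already collected. Confidence is medium.

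**What to change.** In Statistical Method:

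1. Analyse patients in the arm to which they were randomised, with a linear model for the 3-month score adjusted for the baseline score, age and sex. This handles loss explained by those baseline values.
2. Report the number without a 3-month score, and the reasons, by arm.
3. Add a delta-shift tipping-point analysis: make the missing intervention patients worse by δ and state the δ at which significance is lost. With 20% loss in that arm the estimate falls by about 0.20 × δ, so δ = 0.5 SD moves it by 0.10 SD and δ = 1.0 SD by 0.20 SD. Readers can then judge whether such a δ is plausible.

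Multiple imputation from baseline may be the vehicle for step 3, but should not be presented as the remedy. Step 1 should not be adopted without step 3, because the adjusted model can be more biased than the change t-test when loss depends on the 3-month score in one arm.

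The cost is some added wording and modest programming in R, which the plan already uses. The conclusion may become less favourable. The plan is written largely in the past tense and recruitment ended in August 2023, so if the data have already been analysed, these analyses should be labelled post hoc.
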